**Methods/design:**

The aim of our prospective randomised study is to assess the efficacy of the retrograde application of non-selected bone marrow autologous cells concentrate (BMAC) in patients with HFREF of ischemic aetiology. The evaluated preparation is concentrated BMAC, obtained using *Harvest SmartPReP2* (Harvest Technologies, Plymouth, MA, USA). The study population will be a total of 40 patients with established CAD, systolic dysfunction with LV EF of ≤40% and HF in the NYHA class 3. Patients have been on standard HF therapy for 3 months and in a stabilised state for at least 1 month, before enrolling in the clinical study. Patients will be randomised 1:1 to either retrograde BMAC administration via coronary sinus or standard HF therapy. The primary end-points (left ventricular end-systolic and end-diastolic diameters [LVESd/EDd] and volumes [LVESV/EDV] and left ventricular ejection fraction [LV EF]) will be assessed by magnetic resonance imaging. The follow-up period will be 12 month.

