## Methods/design

The study population will be a total of 40 patients with established CAD and left ventricular systolic dysfunction with an EF of ≤40% and HF in the NYHA class 3. CAD will be demonstrated based on previous coronary angiography (myocardial infarction > 6 months, presence of significant coronary stenosis, previosu revascularisation) or Tc SPECT (perfusion defects). The patient follow-up duration will be 12 months.

Patients have been on standard HF therapy for 3 months and in a stabilised state for at least 1 month, before enrolling in the clinical study. A list of inclusion and exclusion criteria is provided in Table 1.

**Table 1 Tab1:** Inclusion and exclusion criteria

Inclusion criteria:	
• Patients with chronic heart failure and left ventricular ejection fraction ≤40% with coronary artery disease and with symptoms of heart failure in the NYHA class 3 on standard heart failure therapy for 3 months and in a stabilised state for at least 1 month,	
• Age 40–80 years	
• Informed, written consent by the patient	
• Ability to comply fully with the study protocol	
• Negative pregnancy test (and effective contraception) in women with childbearing potential	
Exclusion criteria:	
• Previous bone marrow disease (especially myelodysplastic syndrome or non-Hodgkin’s lymphoma)	
• Repeated acute coronary syndrome <1 month	
• CRT device with LV lead in CS	
• Active infection or ATB treatment <1 week	
• Previous malignant ventricular arrhythmias without ICD implantation	
• Anemia (HTC ≤ 28%), leukocytosis (≥14.000/mm^3^) or thrombocytopenia (≤50.000/mm^3^)	
• Previous bleeding diathesis	
• Need for hematopoietic growth factor treatment (e.g. erythropoetin, G-CSF)	
• Impossibility of aspiration 240 ml of bone marrow	
• Hepathopathy or cirrhosis (bilirubin, ALT or AST ≥2,5x ULN)	
• Chronic kidney disease >3b stage (eGFR <45 ml/min/1.73m^2^)	
• Uncontrolled hypertension	
• Need for high dose (> 7.5 mg/day) corticotherapy within the next 6 months	
• Inability to stop anticoagulation therapy (> 72 h) before bone marrow aspiration	
• Known malignancies requiring actino or chemotherapy, or previous actinotherapy	
• Patients with a BMI > 40	
• Known allergy to contrast agents	
• Other comorbidities with a life expectancy of 6 months	

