Patients will be randomised 1:1 to one of the following treatment methods: either retrograde BMAC administration via coronary sinus or the control group with standard HF therapy. Patients randomised to the control group will not undergo bone marrow collection, due to ethical reasons. Only standard right heart catheterisation will be performed as sham procedure.

The primary objectives of the clinical study are to improve the LV EF and reduce the LVESd/EDd and LVESV/EDV assessed by magnetic resonance imaging (MRI), and to improve exercise tolerance in the six-minute corridor walk test.

The secondary objectives include identifying the occurrence of severe ventricular arrhythmias according to 24-h ECG Holter monitoring, improving on the NYHA and CCS classes, reducing hospitalisations due to decompenzation of HF, assessing the impact on QoL of patients using the Kanas City Cardiomyopathy Questionare (KCCQ-12) and ensuring the safety of BMAC retrograde administration via coronary sinus by evaluating all adverse events (AE).

All patients will continue on the standard HF treatment during the clinical follow-up (ACE inhibitor/ATII blockers, beta-blockers, MRA, diuretics) and medication necessary for secondary CAD prevention (ASA/clopidogrel, statins). The monitored parameters will be measured echocardiographically in ICD-implanted patients not able to undergo MRI. Patient with cardiac resynchronization therapy (CRT) device (or CRT-ICD) with LV lead placed in CS will not be included. We also not include patients with known contrast allergy.

Written informed consent was obtained from each patient before enrollment in the study. The study protocol complied with the Declaration of Helsinki and was approved by the Ethics Committee of University Hospital Ostrava, Czech Republic. The study was registered at ClinicalTrials.gov (https://clinicaltrials.gov; NCT03372954).

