### Further follow-up

The follow-up visits will be performed according to the protocol after 1, 3, 6 and 12 months (Visits 3, 4, 5 and 6) **[**Table 2**]**, and a physical examination as well as 12 lead ECG and laboratory tests (blood count + diff, clinical biochemistry, troponin I and NT-pro-BNP) will be performed during each visit and any AEs (cardiovascular death, hospitalisation due to decompensation of HF, acute MI, etc.) recorded. An echocardiographic examination will be performed during screening, and MRI examinations will take place on enrolment (Visit 1) and on the final Visit 6 in month 12. LV parameters and a percentage of total myocardial scar (TMS%) and peri-infarct border zone (PI%; PI = 2–3 SD) will be measured using delated myocardial enhancement assessment [5].

In addition, 24-h Holter ECG monitoring will be performed on enrolment (Visit 1) and after 1 month (Visit 3). Exercise tolerance using a six-minute corridor walk test and QoL (KCCQ-12) will be monitored prior to enrolment (Visit 1) and after 6 (Visit 5) and 12 months (Visit 6) **[**Table 2].

Interventional cardiologists will not be blinded to the assigned therapy, but clinical evaluation, measurement of MRI parameters and data processing will be performed by blinded, independent persons.

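### Primary LV endpoints are defined by MRI but measured by echocardiography in some ICD patients, with no rule that a patient's two values share a modality and no account of modality in the stated analysis

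*Protocol article*

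**What the plan says.** **Endpoint.** The abstract says the LV diameters, "volumes [LVESV/EDV] and left ventricular ejection fraction [LV EF]) will be assessed by magnetic resonance imaging", with no exception. The primary objectives in Methods/design repeat this: "improve the LV EF and reduce the LVESd/EDd and LVESV/EDV assessed by magnetic resonance imaging (MRI").

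**Substitution.** Later in Methods/design: "The monitored parameters will be measured echocardiographically in ICD-implanted patients not able to undergo MRI". Table 2 has a single combined MRI/ECHO row, marked at Visit 1 and Visit 6.

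**Who this affects.** ICD carriers are eligible. Table 1 excludes "Previous malignant ventricular arrhythmias without ICD implantation", so such an arrhythmia is no bar once an ICD is in place. The only device exclusion is CRT with an LV lead in the coronary sinus.

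**Timing.** Further follow-up says: "An echocardiographic examination will be performed during screening, and MRI examinations will take place on enrolment (Visit 1) and on the final Visit 6". That sentence places echo at screening only and does not mention the month-12 echo that the substituted patients would need.

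**Blinding.** The same section says "clinical evaluation, measurement of MRI parameters and data processing will be performed by blinded, independent persons". Echo readings are not named.

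**Analysis.** Sample size and statistical analysis compares normally distributed continuous variables by Student's two-sample t test and the rest by Mann–Whitney U. It does not say whether month-12 values or changes are compared, and it names no modality term or stratum.

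**The concern.** The endpoint is given as MRI in one place, as MRI with echo substitution in another, and as MRI/ECHO in a third. If the plan is followed as written, echo and MRI values of the same parameter enter one unadjusted comparison. Two methods of measuring ventricular volume need not agree on level or precision.

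There are three ways in which this can reach the result:

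- **Raw month-12 values.** A level difference between methods adds variance, and a chance imbalance between the arms in the share of echo patients shifts the arm difference.
- **Change from baseline with a switch.** A patient who receives an ICD after the Visit 1 MRI could have an MRI baseline and an echo at month 12. The offset then enters that patient's change.
- **Change from baseline, one method throughout.** A constant offset cancels, but if echo is noisier the variance still rises.

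The trial has little reserve: 17 per group needed, and 18 expected from 20 after 10% loss. Leaving the method and the analysis set open also leaves a choice that could be made after the data are seen.

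**Working it through.** **Inputs from the article** (Sample size and statistical analysis): LVESV difference 13.0 ml; SD 12.9 ml, reading the printed 13.0 + 12.9 as difference ± SD; alpha 5%, taken as two-sided; power 80%; 17 per group; 10% loss; 20 per arm.

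**Inputs not in the article, so assumed:** the share p of patients measured by echo (or switching), the echo–MRI offset b in LVESV, and the ratio r of echo SD to MRI SD.

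**1. The plan's own figure.** Standardised effect = 13.0/12.9 = 1.008. The t test needs 16.5, so 17 per group, with power 81.3% at 17 and 83.6% at 18. The stated 17 reproduces. Inflating for loss, 17/0.9 = 18.9, so 19 per arm; the stated 20 covers it. The sample size arithmetic is not in dispute.

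**2. Raw month-12 values, share p on echo.** The planning SD of 12.9 ml is used as the single-modality SD.

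SD′ = √(12.9² + p(1 − p)b²)

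With p = 0.30 and b = 20 ml: √(166.4 + 0.21 × 400) = √250.4 = 15.8 ml. Power at 17 per arm is 64%, and 25 per arm would be needed for 80%.

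Over a wider assumed range at 17 per arm:

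| Echo share | Offset | SD′ | Power |
|---|---|---|---|
| 10% | 10 ml | 13.2 ml | 79% |
| 30% | 10 ml | 13.7 ml | 77% |
| 30% | 20 ml | 15.8 ml | 64% |
| 30% | 30 ml | 18.9 ml | 50% |
| 50% | 30 ml | 19.8 ml | 46% |

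**3. Chance imbalance in the same setting.** SD of the shift in the arm difference = b√(2p(1 − p)/17). For p = 0.30, b = 20: 20 × √(0.42/17) = 3.1 ml. Across the range in the table it is 1.0 to 5.1 ml, against a 13 ml target. This is the same variance as in step 2 seen another way, not an additional loss.

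**4. Change from baseline, one patient in 18 switching.** p(1 − p) = (1/18)(17/18) = 0.0525. With b = 20 ml: √(166.4 + 21.0) = 13.7 ml. Power at 18 per arm falls from 84% to 79%.

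**5. Change from baseline, same method at both visits.** The offset cancels and power at 17 per arm stays at 81% unless echo is noisier. If it is, SD′ = 12.9√(1 − p + p r²). With p = 0.30 and r = 1.5: 12.9 × √1.375 = 15.1 ml, power 68%. With p = 0.20 and r = 1.5 it is 72%; with p = 0.50 and r = 2 it is 44%.

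Steps 2 and 3 belong to a different analysis from steps 4 and 5. Their losses should not be added together.

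**The case against.** The strongest reply is that the article sets the method by patient. An ICD carrier enrolled as such would naturally have echo at both Visit 1 and Visit 6, so in a change analysis a constant offset drops out. Mixing within a patient then needs an ICD implanted during follow-up, and the screening echo already gives a baseline to pair with. This largely stands. What remains is that neither the same-method rule nor a change analysis is written down.

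It is also fair that pooling is inferred from the combined table row and the generic test description, that no share of ICD patients or echo–MRI offset is given anywhere, and that covariates and sensitivity analyses are often left to an analysis plan, which is not shown here. The inconsistent endpoint definition, however, is in this document.

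Three stronger readings are tempting, and the documents do not support them:

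- **Systematic bias.** Modality would bias the comparison only if its use, or switching, differed by arm. Nothing shows that; 1:1 randomisation leaves noise and chance imbalance.
- **A contradiction with the MRI drop-out counted in the 10% loss.** Echo is offered only to ICD patients who cannot have MRI. A patient without an ICD and without a usable month-12 MRI has no fallback and can properly be counted as lost.
- **Echo read unblinded.** The blinding sentence also covers clinical evaluation and data processing, which may include echo. The point is only that echo readings of a primary endpoint are not named.

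**Conclusion.** The point holds as a should-fix. The primary LV endpoints are defined by MRI in one place and by MRI or echo in another, and the stated analysis neither requires one method per patient nor takes account of method.

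The size depends on assumptions that the documents cannot settle. Comparing raw month-12 values with 30% echo and a 20 ml offset would take power at 17 per arm from 81% to about 64%. A single switch in 18 with the same offset would cost about 5 points at 18 per arm (84% to 79%). With one method per patient and changes analysed, a constant offset costs nothing, and only extra echo noise matters. All of these figures treat 12.9 ml as the single-modality SD of whatever quantity is analysed, and use a two-sided t test.

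A reader might infer that the trial is underpowered or its result biased. Neither follows: the planned size reproduces, and no mechanism tied to treatment arm is shown.

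**What to change.** 1. State the endpoint in the same words in the abstract, Methods/design, Table 2 and Further follow-up: MRI, or echocardiography where an ICD prevents MRI, and include the month-12 echo in the visit text.
2. Make the analysed quantity the change from baseline to month 12, with both values from the same method. If MRI becomes impossible during follow-up, pair the month-12 echo with the screening echo.
3. Compare arms with adjustment for baseline and with modality as a single covariate.
4. Report an MRI-only sensitivity analysis.
5. Say that echo readings of the primary endpoint are also made by blinded, independent readers.

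**Cost.** Wording, one extra model term in a trial of 40, and complete LV diameters, volumes and EF recorded at the screening echo so that it can serve as a baseline. The MRI-only analysis will have fewer patients and less power, so it can only support the main result. Stratifying randomisation by expected modality is optional at this size.

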### The course of clinical study

The course of the clinical study is illustrated in Fig. 1 and Table 2.

**Fig. 1 Fig1:**
[figure not shown]
CONSORT study flow diagram

**Table 2 Tab2:** SPIRIT overview of study visits and procedures

	Study Period					
	Enrolment	Allocation	Post-allocation			Close-out
	Visit 1	Visit 2	V3	V4	V5	Visit 6
Timepoint	-1 month	0	1 M	3 M	6 M	12 month
Enrolment						
Eligibility screen	X					
Informed consent	X					
Biochemistry	X	X		X	X	X
Blood count	X	X		X	X	X
NT-pro BNP	X	X		X	X	X
CK-MB, troponin I	X	X		X	X	X
ECG	X	X	X	X	X	X
Allocation		X				
Interventions						
BMAC application		X				
Standard HF therapy		X				
Assessments						
MRI/ECHO	X					X
LVESd/LVEDd	X					X
LVESV/LVEDV	X					X
LV EF	X					X
TMS%; PI%	X					X
Corridor walk test	X				X	X
24-h ECG Holter	X		X			
Kanas City Cardiomyopathy Questionare	X				X	X

### Aspiration and preparation of bone marrow autologous cells concentrate (BMAC)

Bone marrow aspiration will be performed in local anesthesia with lidocaine and analgosedation with propofol or midazolam using a Yamshidi aspiration needle, and 240 ml of bone marrow will be aspirated and collected in an ACD-A transfer bag. A sample of 5 ml will be taken to assess the baseline count of nuclear cells.

The aspirate will be transferred to centrifuge bottles to produce BMAC, using the *Harvest SmartPReP2* instrument. Next, 2 ml of 8.4% bicarbonate will be added to the obtained concentrate, to adjust pH, and 18 ml of the patient’s plasma – the original 240 ml of aspirate will thus produce a total of 60 ml of BMAC. Quantitative and qualitative analyses of 5 ml of bone marrow aspirate (BMA) and 5 ml of BMAC will be perormed to assess the cellular composition and content of CD43+ cell. The remaining part of the concentrate will be transferred to opaque 10 ml syringes for application.

### Retrograde administration procedure

Coronary sinus cannulation will be performed via the femoral vein under standard conditions. The diameter of the coronary sinus will be measured using contrast medium injection. An *Advance CS* (Cook, Bloomington, IN, USA) balloon catheter of appropriate size will then be inserted onto a 0.035″ guide wire and inflated (at a maximum pressure of 2 atm), and a small amount of contrast medium will be administered to confirm sufficient coronary sinus occlusion. The total volume of 60 ml of BMAC preparation, divided into 10 ml injection vials, will be infused into the coronary sinus during over a five-minute period. Subsequently, the balloon catheter will remain inflated for 10 min, to allow cells to migrate to cardiac tissue. After this procedure, patients will be hospitalised for a minimum of 24 h, with ECG and vital signs monitoring.

### Further follow-up

The follow-up visits will be performed according to the protocol after 1, 3, 6 and 12 months (Visits 3, 4, 5 and 6) **[**Table 2**]**, and a physical examination as well as 12 lead ECG and laboratory tests (blood count + diff, clinical biochemistry, troponin I and NT-pro-BNP) will be performed during each visit and any AEs (cardiovascular death, hospitalisation due to decompensation of HF, acute MI, etc.) recorded. An echocardiographic examination will be performed during screening, and MRI examinations will take place on enrolment (Visit 1) and on the final Visit 6 in month 12. LV parameters and a percentage of total myocardial scar (TMS%) and peri-infarct border zone (PI%; PI = 2–3 SD) will be measured using delated myocardial enhancement assessment [5].

In addition, 24-h Holter ECG monitoring will be performed on enrolment (Visit 1) and after 1 month (Visit 3). Exercise tolerance using a six-minute corridor walk test and QoL (KCCQ-12) will be monitored prior to enrolment (Visit 1) and after 6 (Visit 5) and 12 months (Visit 6) **[**Table 2].

Interventional cardiologists will not be blinded to the assigned therapy, but clinical evaluation, measurement of MRI parameters and data processing will be performed by blinded, independent persons.

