### Sample size and statistical analysis

The statistical estimate of the size of the file was based on the data from previous studies in patients with congestive heart failure [6] in which was reached the difference of 13.0 + 12.9 ml in LVESV between study and control groups. α type I error of 5%, and β test strength of 80% were used to determine the required group size of 17 patients per group. When including an expected loss of 10% of patients in the 12-month follow-up (including MRI drop out), the resulting size of our group was 40 patients (20 per arm).

Continuous variables with normal distribution will be presented as mean and standard deviation (SD) and will be compared using Student 2-sample *t* test. Continuous variables with non-normal distribution will be presented as the median and range (minimum–maximum or lower and higher percentile) and will be compared using the nonparametric Mann–Whitney *U* test. Categorical variables will be presented as counts and percentages and will be compared using the χ2 or Fisher exact test. Odds ratios (OR) are expressed with 95% CI. A *p* < 0.05 will be considered significant. All statistical analyses will be performed using IBM SPSS Statistics version 22.

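### The six-minute walk, listed as a primary objective, is measured at months 6 and 12, but the stated two-sample test names no deciding visit and makes no use of baseline as a covariate

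*Protocol article*

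**What the plan says.** - **Status of the walk.** The primary objectives in Methods/design are the MRI measures "and to improve exercise tolerance in the six-minute corridor walk test". The Abstract lists only the left ventricular measures as primary end-points, which "will be assessed by magnetic resonance imaging. The follow-up period will be 12 month".
- **Status of KCCQ-12.** It is a secondary objective: "assessing the impact on QoL of patients using the Kanas City Cardiomyopathy Questionare (KCCQ-12".
- **Timing.** Further follow-up states: "a six-minute corridor walk test and QoL (KCCQ-12) will be monitored prior to enrolment (Visit 1) and after 6 (Visit 5) and 12 months". Table 2 agrees. MRI has a single post-baseline time, month 12.
- **Analysis.** Under Sample size and statistical analysis, normally distributed continuous variables "will be compared using Student 2-sample" t test, and the others "will be compared using the nonparametric Mann–Whitney" U test. A p value "< 0.05 will be considered significant".
- **Not stated.** The article does not say which visit decides the walk objective, whether values or changes from baseline are compared, or how two visits share the 5%.

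**The concern.** A two-sample test takes one number per patient. For the left ventricular measures the schedule settles which number, because there is one follow-up MRI. For the walk and KCCQ-12 there are two candidates and nothing chooses between them. The deciding visit is part of the definition of the endpoint, so an objective called primary has an open success criterion.

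Two things are at stake. First, a claim could rest on whichever visit reaches p < 0.05. Second, the stated tests leave information unused: neither takes baseline as a covariate, and a month-12 two-sample test makes no use of the month-6 value of a patient lost afterwards. With 20 patients per arm, that information is worth having.

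**Working it through.** **1. The plan's own figure.** The plan states: "α type I error of 5%, and β test strength of 80% were used to determine the required group size of 17 patients per group". The inputs are a 13.0 ml difference in LVESV, with 12.9 ml read as the SD (an assumption about the printed expression), and a two-sided 5% level (sidedness is not stated). Exact t-test power is 0.788 at 16 per group and 0.813 at 17, so 17 reproduces. Allowing for 10% loss, 17/0.9 = 18.9, or 19 per arm and 38 in total; the plan's 40 is within two patients. The calculation rests on LVESV alone, so nothing below changes it. For the walk I use 20 per arm with 2 lost (10%), leaving 18 at month 12.

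**2. Two visits at 5% each.** The article gives no correlation, so I assume a range. With r the correlation of the two test statistics, the chance under the null of at least one |z| > 1.96 is 1 − P(|Z₁| ≤ 1.96 and |Z₂| ≤ 1.96):

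| r | chance of at least one false positive |
|---|---|
| 0 (independent) | 1 − 0.95² = 9.75% |
| 0.5 | 9.1% |
| 0.7 | 8.3% |
| 0.8 | 7.8% |
| 0.9 | 7.0% |

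Simulated t tests with 17 to 20 per arm gave 7.0% to 9.2% over r = 0.9 to 0.5. One named visit keeps this at 5%.

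**3. Precision at month 12.** Assumed correlations are 0.7 (baseline to month 6), 0.6 (baseline to month 12) and 0.8 (month 6 to month 12). Loss is 2 per arm at random after month 6. Large-sample standard errors, in SD units:

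- t test on values: √(2/18) = 0.333.
- t test on change: variance 2(1 − 0.6) = 0.8, so √(0.8 × 2/18) = 0.298.
- Month-12 analysis adjusted for baseline, ignoring month 6: residual variance 1 − 0.6² = 0.64, so √(0.64 × 2/18) = 0.267.
- Repeated-measures model: the partial correlation of months 6 and 12 given baseline is (0.8 − 0.7 × 0.6)/√(0.51 × 0.64) = 0.665. The variance shrinks by the factor 1 − 0.665² × 2/20 = 0.956, and the SE by 0.978, giving 0.261.

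Simulation (20,000 trials) gives 0.334, 0.298, 0.272 and 0.266. The last two are slightly above the formula because coefficients are estimated in a small sample. Baseline adjustment takes the SE from 0.33 to 0.27; the month-6 data contribute the last 2% or so.

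**4. Loss related to the month-6 walk.** As a deliberately extreme pattern, remove the two worst month-6 walkers from the control arm and nobody from the BMAC arm. The bias in BMAC minus control at month 12 is −0.15 SD (t test on values), −0.02 SD (t test on change), −0.07 SD (baseline-adjusted, month 6 ignored) and 0.00 SD (repeated-measures model).

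**The case against.** The strongest reply is that the article condenses a fuller protocol. A mixed model, its covariance structure and the handling of lost patients are commonly left to the analysis plan, and a two-sample test at one visit is a valid randomised comparison. Follow-up is 12 months, the MRI is at month 12 and the sample size uses 12-month loss, so month 12 is the natural deciding visit. That stands as far as model detail goes: the absence of those details is not an error. It does not settle the visit, because the article states the test and threshold for every continuous variable and leaves a twice-measured objective without its time point.

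A reader might infer more than the article supports:

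- **That both visits will be tested.** The text does not say so. It leaves the possibility open.
- **That month-6 data are discarded.** The text does not say this either. If both visits were tested, the month-6 values of patients lost later would enter the month-6 comparison. They are unused only in the month-12 comparison.
- **That the narrower interval comes from the month-6 data.** Almost all of it comes from baseline adjustment.
- **That a bias of −0.15 SD is to be expected.** That figure needs raw month-12 values and an extreme loss in one arm. With changes from baseline it is about −0.02 SD, and its direction works against BMAC. The planned 10% loss also includes MRI drop-out, and such patients may still walk at month 12.

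**Conclusion.** The point holds in limited form. Methods/design calls the walk a primary objective, the schedule gives it two follow-up values, and the stated single-time-point test comes with no deciding visit and no baseline covariate. This permits a false-positive chance of about 7% to 9% in place of 5%, at assumed correlations of 0.9 to 0.5 and a two-sided level. A baseline-adjusted repeated-measures model would cut the SE of the month-12 difference from about 0.33 or 0.30 SD to about 0.27 SD under the assumed correlations. Protection against outcome-related loss is a further but pattern-dependent benefit.

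The weight is moderate. The Abstract does not count the walk as primary, KCCQ-12 is secondary, and the LVESV-based sample size is untouched. The change is a worthwhile improvement on a stated method, and the stated tests are not invalid.

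**What to change.** Name the month-12 between-arm difference as the test of the six-minute walk objective, and label month 6 supportive. Estimate it, and likewise KCCQ-12, with one repeated-measures model per measure:

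- terms for treatment, visit (6, 12), treatment-by-visit, baseline value and baseline-by-visit;
- unstructured covariance between the two visits;
- all randomised patients with any post-baseline value.

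Also align the Abstract and Methods/design on whether the walk is primary.

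The cost is one paragraph of analysis wording. The data are already scheduled, the named SPSS package fits the model, and no visits or patients are added. If the model is not wanted, one sentence naming month 12 as the deciding visit still restores the 5% level, and a month-12 analysis adjusted for baseline recovers most of the precision.
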